### Outcomes

Clinical investigators will obtain written informed consent and collect basic data such as gender, age, height, weight, and medical history at baseline. For safety concerns, besides the basic data, vital signs will be taken and laboratory examinations conducted, for instance, blood pressure, heart rate, routine blood tests (e.g., red blood cell (RBC), white blood cell (WBC), hemoglobin (Hb), etc.), liver and kidney function tests (e.g., ALT, AST, CREA, etc.), pregnancy test, and 12-lead electrocardiogram (ECG). Except for the pregnancy test, which only needs to be conducted in the first visit (week 0, baseline), other tests should be conducted routinely at every visit during the treatment period (the ECG is not mandatory at the second visit (week 4)). Also, any adverse events such as abdominal discomfort should be monitored and recorded during the whole study.

Participants need to receive a blood lipid profile test which contains the following indexes: TC, TG, HDL-C, LDL-C, apolipoprotein A (apoA), apolipoprotein B (apoB), and non-high-density lipoprotein cholesterol (non-HDL-C). The blood sample should be collected after at least a 12-hour fast, and the last meal before the blood sampling should not contain greasy food. In order to evaluate the health status of participants, the MOS 36-Item Short-Form Health Survey (SF-36) is utilized [26–28]. In addition, for assessment of clinical symptoms, another symptomatic grading and quantifying scale is applied. Weight monitoring and diet evaluation are also two aspects that need to be conducted. All participants are required to complete the tests and scales mentioned above at every visit under the guidance and assistance of the clinical investigators. The results are recorded and compared within a group and between groups before and after intervention.

Yirui capsules are designed to act as an intervention method for patients with borderline high serum lipid or an adjunctive choice for patients who could not reach the serum lipid target with conventional therapy. Based on the 2013 American College of Cardiology (ACC)/American Heart Association (AHA) guidelines on the treatment of blood cholesterol [29], the 2007 Chinese guidelines on blood lipid abnormality [30], and a previous TCM clinical trial [31], we set the treatment goal as a 30 % LDL-C decline compared with baseline after intervention. Therefore, the primary outcome is the percentage of participants who reach the goal at treatment endpoint (week 24). Secondary outcomes include the mean changes from baseline at treatment endpoint in LDL-C, TC, TG, HDL-C, apoA, apoB, non-HDL-C, SF-36 scoring, total and individual item scoring of symptomatic grading and quantifying scale, and body mass index (BMI).

Safety and tolerability assessments include collection of adverse events, physical examination, vital signs, and the relevant laboratory examination reported previously. Clinical investigators should observe any adverse events that occur during the clinical trial, including abnormal symptoms and signs, unusual laboratory indicators, etc. Whether or not the adverse event is related to the interventions, investigators are required to record it comprehensively, including onset time, related symptoms and signs, extent, duration, laboratory indexes, treatment, result, and follow-up. In addition, drug combinations should also be documented in order to analyze the correlation between adverse events and experimental products.

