**Table 1 Tab1:**
[figure not shown]
Schedule of enrollment, intervention, and assessments

There will be five visits for each participant in week 0, week 4, week 12, week 24, and week 28. At the first visit, patients will have their general data recorded and will be given the prescription. Then, patients will take the prescription to the specified pharmacy and receive either Yirui capsules or the placebo. 4 weeks and 12 weeks after the first visit, patients will come back for clinical evaluation and medication. Visit 4 is planned for the end of the treatment period (week 24); at this visit patients will only receive clinical evaluation. Afterwards, the patients will stop taking Yirui capsules or the placebo for another 4 weeks and then come back for clinical evaluation.

The study protocol was approved by the ethics committees of the First Affiliated Hospital of Jinan University, Guangdong No. 2 Provincial People’s Hospital, Hexian Memorial Affiliated Hospital of Southern Medical University, and the Fifth Affiliated Hospital, Sun Yat-sen University (Approval Version: LWXJ.YRJN-HBT-V1.0), and informed consent was obtained from each participant.

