#### Inclusion criteria

In this study, the inclusion criteria are as follows: (1) age of 18 to 65 years, both genders; (2) documented blood lipid test results indicated LDL-C ≥3.37 mmol/L complicated with TC ≥5.18 mmol/L, or triglyceride (TG) ≥1.70 mmol/L, or high-density lipoprotein cholesterol (HDL-C) <1.04 mmol/L, or both TC ≥5.18 mmol/L and TG ≥1.70 mmol/L; (3) initial treatment of hyperlipidemia; (4) signed informed consent and agreement to complete all visits, examinations, and treatments.

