#### Exclusion criteria

Patients were excluded for one or more of the following reasons: (1) TG ≥5.65 mmol/L; (2) combined with hypertension, diabetes, or thyroid dysfunction; (3) combined severe primary diseases (i.e., cardiovascular and cerebrovascular diseases, liver and kidney diseases, hematopoietic system dysfunction), or malignant tumor, or mental disorder, or other serious complicated disease; (4) documented hyperlipidemia-induced target organ damage (i.e., atherosclerosis and CHD) with need to maintain treatment to dyslipidemia; (5) secondary hyperlipidemia, drug-induced hyperlipidemia, homozygous hypercholesterolemia; (6) pregnancy; (7) alanine aminotransferase (ALT) and/or aspartate aminotransferase (AST) ≥3 times the upper limit of normal (ULN); (8) creatinine (CREA) ≥1.5 times the ULN; (9) combined with active peptic ulcer or gastrointestinal hemorrhage; (10) allergy to components of product or allergic constitution; (11) hospitalized; (12) cannot obey therapeutic lifestyle modification.

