#### Chinese Medicine intervention

The Yirui capsule is composed of perilla oil, *Folium Ginkgo* (Yinxingye), *Radix Salviae miltiorrhizae* (Danshen), *Fructus Crataegi* (Shanzha), *Rhizoma Alismatis* (Zexie), and *Radix Notoginseng* (Sanqi). The specific Chinese herbal medicine composition and actions are summarized in Table 3. The placebo capsule was a simulant Yirui capsule with a comparable appearance. The main content of the placebo capsule was starch. By adding food colorants and flavoring agents, the mixture achieved a color, smell, taste, and texture comparable to the content of the Yirui capsule. Participants from both the Yirui group and the placebo group were informed to take two assigned capsules orally twice daily for 24 weeks continuously. Both Yirui capsules and the placebo were packed in sealed plastic bottles (120 capsules each). Only the serial number was printed outside the package to ensure successful blinding of patients.

**Table 3 Tab3:** Composition and action of Chinese herbal medicine in Yirui capsule

Ingredients	Action
*Folium Ginkgo*	TCM: Promoting blood circulation to remove blood stasis and stop pain Pharmaceutical study: (1) cardiovascular protective effect, (2) hypolipidemic effect, (3) effect of antagonizing lipid peroxide, (4) effect of improving cerebral circulation
*Radix Salviae miltiorrhizae*	TCM: Promoting blood circulation to remove blood stasis, cooling blood and treating boils, tranquilizing mind Pharmaceutical study: (1) cardiovascular protective effect, (2) hypotensive effect, (3) hypolipidemic effect, (4) anti-inflammatory effect, (5) anti-coagulation effect
*Fructus Crataegi*	TCM: Removing food retention and flatulence, promoting blood circulation to remove blood stasis Pharmaceutical study: (1) gastrointestinal regulation effect, (2) cardiovascular protective effect, (3) hypotensive effect, (4) hypolipidemic effect
*Rhizoma Alismatis*	TCM: Eliminating dampness and diuresis, purging heat Pharmaceutical study: (1) diuretic effect, (2) hypolipidemic effect, (3) anti-allergic effect, (4) anti-inflammatory effect
*Radix Notoginseng*	TCM: Hemostatic elimination of stagnation, promoting blood circulation to stop pain Pharmaceutical study: (1) Anti-coagulation effect, (2) hematopoiesis effect, (3) cardiovascular protective effect, (4) analgesic effect, (5) anti-inflammatory effect

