## Trial status

At the time of manuscript submission, patients are being recruited, and no one has yet completed the treatment.

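### The pregnancy test is required only at week 0, so an early, unnoticed pregnancy can be re-supplied with capsules at week 4 or week 12

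*Protocol article*

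**What the plan says.** All references are to the protocol article.

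- **Outcomes.** The pregnancy test is listed with the safety examinations, and its timing is then fixed: "Except for the pregnancy test, which only needs to be conducted in the first visit (week 0, baseline), other tests should be conducted routinely". The other tests are repeated at each treatment visit, except that the ECG is optional at week 4.
- **Exclusion criteria.** Pregnancy is criterion 6: "homozygous hypercholesterolemia; (6) pregnancy; (7) alanine aminotransferase (ALT".
- **Inclusion criteria.** Women of childbearing age can enter: "1) age of 18 to 65 years, both genders".
- **Chinese Medicine intervention.** Participants are told to "take two assigned capsules orally twice daily for 24 weeks continuously".
- **Study design, visit schedule after Table 1.** Capsules are first supplied after the week 0 visit. Then: "4 weeks and 12 weeks after the first visit, patients will come back for clinical evaluation and medication". At week 24, "at this visit patients will only receive clinical evaluation".
- **Outcomes, safety paragraph.** "Safety and tolerability assessments include collection of adverse events, physical examination, vital signs, and the relevant laboratory examination reported previously".

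**The concern.** The plan treats pregnancy as a reason not to start the capsules, but checks for it once, before a treatment period of 24 weeks. Each later supply is a fresh decision to expose the participant, and at neither re-supply visit does the plan require a check of a condition that would have barred her at entry. Liver enzymes and creatinine, which also define exclusions, are re-measured during treatment. Pregnancy can newly arise after entry, yet its test is expressly exempted from repetition.

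What is at stake is avoidable exposure of an early pregnancy to a multi-component product. The Background says high-quality clinical-trial evidence for this product is still lacking. The estimate of efficacy is not at stake.

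**Working it through.** **Step 1. Is this a stated rule or only a silence?** It is stated. The Outcomes section limits the required test to week 0 in so many words, so condensing a longer protocol into an article does not explain it. A later sentence in that section asks for the tests and scales already mentioned at every visit. It follows the lipid, SF-36, symptom-scale, weight and diet items, and a general sentence of that kind does not displace the specific exception. If it did, the section would contradict itself and would still need correcting.

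**Step 2. Dosing weeks that each supply must cover.** The inputs are supply at weeks 0, 4 and 12, and end of treatment at week 24 with nothing dispensed (Study design). The daily dose is 2 capsules × 2 = 4 (Chinese Medicine intervention). The assumption is that each supply lasts until the next visit.

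| Supply visit | Weeks covered | Duration | Capsules needed (days × 4) | Pregnancy test required? |
|---|---|---|---|---|
| Week 0 | 0 to 4 | 4 weeks | 28 × 4 = 112 | Yes |
| Week 4 | 4 to 12 | 8 weeks | 56 × 4 = 224 | No |
| Week 12 | 12 to 24 | 12 weeks | 84 × 4 = 336 | No |

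The durations sum to 4 + 8 + 12 = 24 weeks, which reproduces the plan's treatment period.

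**Step 3. Is the assumption reasonable?** A bottle holds 120 capsules, or 120 / 4 = 30 days. The three intervals need 112/120 = 0.93, 224/120 = 1.87 and 336/120 = 2.80 bottles, so 1, 2 and 3 whole bottles suffice. This is compatible with supply from visit to visit. The article does not say how many bottles are handed out, so the capsule counts are doses scheduled and not quantities dispensed.

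**Step 4. What would repeat testing change?**

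- Pregnancy detectable at week 4: the 8-week supply is withheld.
- Pregnancy first detectable at week 12: the 12-week supply is withheld.
- Pregnancy not yet detectable at week 12, or beginning later: nothing is withheld.
- Longest stretch of dosing without a required test: 24 weeks as written, and max(4, 8, 12) = 12 weeks with tests at weeks 4 and 12.

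**Step 5. What cannot be computed.** The article gives neither the number of women of childbearing potential nor an expected number of pregnancies, and it documents no reproductive hazard of the product. No count or risk is derived.

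**The case against.** The strongest case for leaving the plan alone has four parts.

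**An entry criterion is checked at entry, which is consistent.** Diabetes and thyroid dysfunction are also exclusions, and the Outcomes section names no repeat test for them. This stands to the extent that the plan does not contradict itself: the point concerns a design choice. But pregnancy can newly arise over 24 weeks and is simple to test for, so the comparison does not justify exempting it.

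**The full protocol may hold contraception rules.** It may, and their absence from an article is no finding. The same goes for pregnancy being missing from the listed reasons for quitting. A reader might infer that the trial has no contraception or pregnancy-withdrawal rules at all; the article does not support that. Such rules would make conception less likely, but a contraception rule would not detect one before a re-supply.

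**Existing safeguards cover part of the problem.** The wording sets a minimum and forbids nothing. Participants are evaluated at weeks 4 and 12, with physical examination and adverse-event recording, and an investigator may test on suspicion. This stands, and it narrows the point to early pregnancies that nobody suspects.

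**Size.** A reader might note that 8 + 12 = 20 of the 24 dosing weeks (83%) are supplied at visits without a required test, and take this as a measure of risk. It is not one. The figure restates the visit schedule and would be the same if no participant could conceive. It also applies equally to men, to women past childbearing and to the placebo arm, whose capsules are mainly starch. Nor should a reader infer that an ingredient is known to harm a pregnancy, since the article says nothing on that.

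**Conclusion.** The point holds as a modest, inexpensive safety improvement. As written, a woman of childbearing potential with an early pregnancy that clinical evaluation does not reveal can be given 8 further weeks of dosing at week 4, or 12 further weeks at week 12, in a state that would have excluded her at entry.

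This rests on two things: that each supply lasts to the next visit, which the schedule and bottle size fit but do not state, and that the body text is the operative rule, since the contents of Table 1 are not shown. The number of women affected is unknown. The primary outcome, power and type I error are unaffected.

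**What to change.** Replace the exception in the Outcomes section with:

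> In women of childbearing potential the pregnancy test is done at week 0 and again before capsules are dispensed at weeks 4 and 12; capsules are not dispensed if it is positive.

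Table 1 should be brought into line if it shows week 0 only. No week 24 test is proposed, because no capsules are supplied then.

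**Cost.** Up to two added tests per woman of childbearing potential, at visits where blood is already drawn, with no extra visit. The ceiling is 2 × 180 = 360 tests if every planned participant were such a woman; the true number will be lower. An ethics amendment is needed at the four centres. At submission, "patients are being recruited, and no one has yet completed the treatment", so the change could still help those with a week 4 or week 12 supply ahead of them.

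**Limit.** A 12-week stretch after the week 12 supply remains without a required test, so a conception not detectable by then is not caught.

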### Data collection and handling of withdrawal and dropout

In this 28-week clinical trial, it is compulsory for participants to take experimental medication for a continuous 24 weeks, be present at five assessment visits, conduct several blood tests, finish certain scales, complete a diet evaluation diary card, and stop taking other lipid-lowering medication and drugs with relevant herbal ingredients. Specially assigned individuals will record the original data, and the relevant materials will be placed on file based on numerical order at the specified site appropriately. Only principal investigators and clinical investigators have the right to examine the documents. Original documents should be preserved at least 5 years after finishing the study.

For maximum compliance of patients, we require all researchers and doctors to obey the following rules. Firstly, all researchers should obey the principle of informed consent and help participants understand the requirements of the study. Secondly, researchers need to monitor the compliance of patients through the dose counting method. Thirdly, all doctors should ask patients to bring all medications to every visit to examine and record any drug combinations. Moreover, investigators will contact the participant to remind them of the visit three days in advance and to inform them of the specific arrangements for the next visit. For patients who do not respond to the medication or cannot take medication on time, increasing the frequency of the follow-up visits is compulsory.

Participants can quit the study if they experience: (1) severe adverse effect(s), (2) hypersensitivity towards the research medication, or (3) aggravation of disease. The whole research plan will be terminated for the following circumstances: (1) presence of serious adverse events related to the research medication, (2) no practical value findings of the medication during the treatment, or (3) completion of all follow-up assessments.

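### SF-36 and the symptom scale, both subjective secondary outcomes, are completed with help from investigators who may know earlier lipid results; self-completion at the start of the visit would close this route

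*Protocol article*

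**What the plan says.** The Outcomes section of the protocol article lists the lipid profile, SF-36, a symptom scale, weight monitoring and diet evaluation. It then says of all of them together: "All participants are required to complete the tests and scales mentioned above at every visit under the guidance and assistance of the clinical investigators". The same section names "SF-36 scoring, total and individual item scoring of symptomatic grading and quantifying scale" among the secondary outcomes, analysed as mean change from baseline to week 24. The primary outcome is the share of participants whose LDL-C has fallen by 30 % at week 24.

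Two statements under Data collection and handling of withdrawal and dropout bear on what site staff may know. The first is "For patients who do not respond to the medication or cannot take medication on time, increasing the frequency of the follow-up visits is compulsory". The second, on the original records, is "Only principal investigators and clinical investigators have the right to examine the documents".

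Assignment and blinding keeps patients and clinical investigators unaware of treatment until the study is over. It also has both complete a guess-the-treatment questionnaire at the last visit.

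**The concern.** SF-36 and the symptom scale depend on how the participant judges and reports his or her own state. The article fixes who helps with them and puts no limit on that help. If the helper knows that a participant's LDL-C has fallen, encouragement or interpretation can nudge the answers upwards without any intent to do so.

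Matching capsules and concealed allocation guard against knowing the treatment. They do not guard against knowing the response. If the product lowers LDL-C, visible responders will be more frequent in the Yirui arm. A nudge given to responders in either arm then appears as a difference between arms in quality of life and symptoms that the capsule did not cause. A favourable result on these scales would be open to that explanation, and the blinding questionnaire could reveal guessing but could not repair scores already collected.

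**Working it through.** The plan states no figure on this point, so there is none to reproduce. The check has two parts.

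**Can the helper know the response?** The relevant texts, side by side:

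- Outcomes: the lipid profile is among the tests done at every visit, so week 4 and week 12 results exist before the week 24 scales are completed.
- Data collection and handling of withdrawal and dropout: extra visits for patients who do not respond require someone at the site to judge response. The term is not defined there. The only treatment goal in the article is the 30 % LDL-C fall.
- Same section: clinical investigators may examine the original documents. The article states no restriction on lipid results.

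Knowledge of earlier results is therefore plausible, but it is inferred. Nothing shows that the week 24 result is back when the week 24 scales are filled in.

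**How much could it matter?** Inputs:

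- Responder rates 0.10 (placebo) and 0.30 (Yirui), from Sample size calculation. These are week 24 rates; no rates are given for weeks 4 and 12, so they serve as an approximation.
- Allocation 1:1, from Assignment and blinding.
- Two-sided 5 % level, from Statistical analysis.
- 90 per arm randomised, 75 before the dropout allowance, from Sample size calculation. Intention-to-treat analysis with last observation carried forward points to 90.
- Shift s, in SD units, in the scores of perceived responders: assumed. The documents give none.

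What response reveals about the arm:

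- P(Yirui | responder) = 0.30 / (0.30 + 0.10) = 0.75
- P(Yirui | non-responder) = 0.70 / (0.70 + 0.90) = 0.4375
- Correct guesses, calling responders Yirui and the rest placebo: 0.5 × 0.30 + 0.5 × 0.90 = 0.60, against 0.50 by chance

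Bias between arms = s × (0.30 − 0.10) = 0.20 × s.

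Standard error of the difference = √(2/n): 0.149 SD at 90 per arm, 0.163 SD at 75.

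False-positive rate when the capsule has no effect on the scale = 1 − Φ(1.96 − bias/SE) + Φ(−1.96 − bias/SE).

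| Assumed s (SD) | Bias (SD) | 90 per arm | 75 per arm |
|---|---|---|---|
| 0.25 | 0.05 | 6.3 % | 6.1 % |
| 0.5 | 0.10 | 10.3 % | 9.4 % |
| 1.0 | 0.20 | 26.9 % | 23.2 % |

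Example at s = 0.5 and 90 per arm: 0.10 / 0.149 = 0.671, so 1 − Φ(1.289) + Φ(−2.631) = 0.099 + 0.004 = 0.103. The formula ignores the extra spread that the shift itself adds, which makes the largest case somewhat too high.

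**The case against.** The strongest case against the point is that it rests on supposition.

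- The sentence on assistance covers blood tests and scales together and says that participants complete them. It does not say that investigators choose, suggest or score answers, and supervised completion is ordinary practice.
- The non-response provision sits in a paragraph about compliance and does not mention LDL-C.
- Investigators and patients are blind to allocation, and the success of blinding is assessed.
- The order of procedures and the routing of laboratory reports are commonly left to a full protocol, which is not shown here.

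Most of this stands, and it limits the point. A reader might infer that the helpers follow each participant's LDL-C and know it when the scales are filled in. The documents do not say that; they only make it possible for earlier results. A reader might also take 10 % or 27 % as the trial's actual error rate. Those figures need every perceived responder to be shifted by 0.5 or 1 SD, and they apply week 24 responder rates to what is known at weeks 4 and 12. At a shift of 0.25 SD the rate hardly moves from 5 %.

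The appeal to an unseen full protocol does not remove the point. The article states the procedure, namely investigator guidance and assistance without limit, and that stated procedure can be improved. Nor does blinding to allocation answer it, because response carries some information about the arm even when allocation is masked.

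**Conclusion.** The point holds as a minor one. The stated procedure leaves an avoidable route by which knowledge of lipid response could colour two subjective secondary outcomes. Any such effect is diluted to about one fifth of the steering, which makes the false-positive rate at 90 per arm about 6 % to 27 % for assumed shifts of 0.25 to 1 SD. The range rests on three assumptions: that helpers know earlier lipid results, that they shift perceived responders' scores by the stated amount, and that the plan's 30 % and 10 % apply when the help is given. None of these is established by the documents.

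A reader might extend the concern to the trial's efficacy conclusion as a whole. That would be wrong: the primary outcome is a laboratory LDL-C threshold, and neither it nor the sample size built on it is touched by how the scales are completed.

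**What to change.** Amend the sentence in Outcomes so that it no longer covers tests and scales alike. Have participants complete SF-36 and the symptom scale themselves at the start of each visit, before clinical contact or discussion of results. Limit any help to reading items aloud, preferably by existing staff who have not seen the lipid results.

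The cost is a small change in visit order and less help for participants who find the scales difficult. No endpoint, sample size or analysis changes. Trial status records that nobody had completed treatment at submission, so at that stage the change could still have applied to all week 24 assessments.

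Withholding lipid results from investigators is not required. If the sponsor wants it, it must first be reconciled with the provision on patients who do not respond under Data collection and handling of withdrawal and dropout.
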